### Procedure for unblinding if needed {17b}

COG-EYE is an open-label trial; thus, the participants, caregivers, principal investigator, and all research staff will not be blinded.

## Data collection and management

### Plans for assessment and collection of outcomes {18a}

All research staff will be trained in the acquisition of eye-tracking metrics and digital pen data. The MMSE, CDR, GDS, S-IADL, and VOSP will be performed by authorized clinical psychologists. The assessments will be performed based on the study schedule.

Eye-tracking will be recorded during the copying of the simplified RCFT. After standard gaze mapping, we will quantify eye-tracking metrics such as the number and duration of fixations, saccades, and switching between perception and working areas. These quantified metrics will be compared between the donepezil and control groups.

The digital pen trajectory will be recorded during the copying of the simplified RCFT. After preprocessing, we will quantify digital pen data, such as pen stroke, drawing boundary, and drawing area. These quantified metrics will be compared between the donepezil and control groups.

If the parametric test requirement is not satisfied with the missing data, a non-parametric test will be used.

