**Fig. 2 Fig2:**
[figure not shown]
COG-EYE schedule of enrolment, interventions, and assessments**.** CDR, Clinical Dementia Rating; ECG, echocardiography; GDS, Global Deterioration Scale; MMSE, Mini-Mental State Examination; MRI, magnetic resonance imaging; PET, positron emission tomography; S-IADL, Seoul-Instrumental Activities of Daily Living; TC, telephone consultation; V, visit; VOSP, visual object and space perception battery

During the screening visit, blood samples (for analyses of thyroid function, folic acid, and vitamin b12; syphilis screening; and apolipoprotein E genotyping), echocardiography (ECG), neuropsychological test battery, brain MRI, and amyloid PET will be collected. These results are needed to screen for other causes of cognitive impairment and to only recruit patients with MCI in the Alzheimer’s continuum.

Allocation will occur after baseline screening. Donepezil will be packed with clear dosing instructions and schedule. At visit 1, detailed baseline assessments will be required of all participants. Then, participants allocated to the donepezil group will be instructed to consume a dose of 5 mg once daily for the first 4 weeks. The participants allocated to the control group will not be administered donepezil during the study period. At visit 2, follow-up assessments of the measures of efficacy, except for VOSP, and detailed reporting of potential adverse effects will be required of all participants. Participants allocated to the donepezil group will then be instructed to increase the dose to 10 mg once daily for the next 8 weeks. At visit 3, follow-up assessments, including all measures of efficacy performed at baseline, and detailed reporting of potential adverse effects will be required of all participants.

V1, V2, and V3 measurements will be acquired with the following means.1. Eye-tracking metrics during the simplified RCFT and CDT on a digital tablet.2. MMSE3. CDR4. GDS5. S-IADL6. VOSP (VOSP is not performed at V2).7. Digital pen data during simplified RCFT copying test on digital tablet [13]

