#### Criteria for discontinuing or modifying allocated interventions {11b}

Study intervention may need to be discontinued or modified due any of the following reasons.1. Allergic reaction to the medication.2. An adverse event which requires discontinuation of the trial medication or results in inability to continue to comply with trial procedures.3. Violation of inclusion/exclusion criteria or significant protocol violation.4. Withdrawal of consent.5. Significant nonadherence to treatment regimen or trial requirements6. The investigator determines that the participant has to discontinue.

In the case of withdrawal from the clinical trial, the administration of the medication should be stopped, and the date of discontinuation, reasons, and findings should be recorded in the CRF, along with all the results of the trial obtained until the time of withdrawal. In the case of exclusion from clinical trials due to clinically significant laboratory abnormalities, follow-up will be conducted for a period determined to be reasonable or until the relevant event or laboratory abnormality is resolved.

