#### Prohibited medication

 The medications to be prohibited during the clinical trial period are as follows; if a participant uses contraindicated medications, participation in the clinical will be stopped.1. Other ChEIs: rivastigmine, galantamine.2. NMDA receptor antagonist: memantine.

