## Assignment of interventions: blinding

### Who will be blinded {17a}

COG-EYE is an open-label trial; thus, participants, caregivers, principal investigator, and staff will not be blinded.

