### Plans to promote participant retention and complete follow-up {18b}

Participants will be in close contact with each other. There will be scheduled safety checks and frequent contact with the research staff as per the participants’ wish. All randomized participant data will be included in the analysis. If participants withdraw from the study at any stage, they will be asked whether their data accumulated at the point of withdrawal could be included.

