### Methods in analysis to handle protocol non-adherence and any statistical methods to handle missing data {20c}

Missing data will be sought and supplemented where possible after consultation with the investigator.

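### The primary test uses only participants with a week-12 value, which cannot deliver the promised analysis of all randomised, and the plan does not secure week-12 data after stopping or use the week-4 eye-tracking

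*Protocol article*

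**What the plan says.** - **Outcome and test.** Outcomes {12} defines the primary outcome as the change in the fixation ratio (working space over perceptual space) from baseline to 12 weeks. Statistical methods {20a} assigns it a two-sample t-test. There, the choice between t-test and Mann–Whitney according to normality is given for continuous secondary outcomes only. The Abstract allows either test for primary and secondary outcomes alike.
- **Fallback.** Plans for assessment and collection of outcomes {18a}: "If the parametric test requirement is not satisfied with the missing data, a non-parametric test will be used".
- **Missing data.** The whole of section {20c} reads: "Missing data will be sought and supplemented where possible after consultation with the investigator". Section {17a} states: "COG-EYE is an open-label trial; thus, participants, caregivers, principal investigator, and staff will not be blinded".
- **Who is analysed.** Section {18b}: "All randomized participant data will be included in the analysis". Of those who withdraw, the next sentence says: "they will be asked whether their data accumulated at the point of withdrawal could be included".
- **Stopping.** Section {11b} lists reasons for discontinuing or modifying the intervention (allergy, adverse event, eligibility violation, withdrawn consent, non-adherence, investigator decision). On withdrawal from the trial, the date, reasons and findings are then recorded, "along with all the results of the trial obtained until the time of withdrawal". Under Prohibited medication: "if a participant uses contraindicated medications, participation in the clinical will be stopped".
- **Week 4.** Intervention description {11a} requires of all participants at visit 2 "follow-up assessments of the measures of efficacy, except for VOSP". Eye-tracking is among these measures.

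**The concern.** A change score to week 12 does not exist for someone with no week-12 recording. A t-test drops that person, and a rank test drops the same person, so the fallback in {18a} does nothing about missingness. The analysed set is then the completers, whatever {18b} promises.

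The stopping provisions may add to the losses. Section {11b} puts reasons to stop the drug in the same list as reasons to leave the trial. The only follow-up it describes afterwards concerns laboratory abnormalities. Controls take no study drug, so allergy to it, intolerance of it and tablet non-adherence arise only under donepezil. If those who leave differ in outcome from those who stay, the comparison is no longer between the groups as randomised. Week-4 eye-tracking could recover part of the lost information, but no analysis uses it.

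**Working it through.** **1. The plan's own figures.** Sample size {14}: standardised effect 0.8, two-sided alpha 0.05, power 90%, attrition 12%. The noncentral t calculation gives n = 33.83, hence 34 per group, with power 90.15% at 34. Inflation: 34/0.88 = 38.6, hence 39 per group and 78 in total. The sample size reproduces. Expected losses are 78 × 0.12 = 9.4, and the design tolerates 39 − 34 = 5 per arm. Power therefore rests on completers.

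**2. The passages side by side.** The primary test needs a week-12 value ({12} with {20a}). The design expects 9 or 10 of 78 without one ({14}). All randomised participants' data are to be analysed ({18b}). These three cannot all hold under a t-test or rank test on change.

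**3. How large the effect could be.** The documents give no dropout pattern, so the patterns below are assumptions. Setting: 39 per arm, no true effect, normal data, three visits with equal correlation ρ of 0.5 or 0.7, control losses at random. *Worst* means the lower tail of change.

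With equal correlations, the two changes from baseline have covariance (1 − ρ)σ² and variance 2(1 − ρ)σ² each. Their correlation is therefore 0.5 for either ρ.

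Removing the lowest 5 of 39 values shifts the mean of the remaining 34 by 0.235 SD. If removal follows week-4 change, the bias in week-12 change is 0.5 × 0.235 = 0.12 SD. The standard error is √(2/34) = 0.243 SD, so the ratio is 0.117/0.243 = 0.48. Type I error is then about P(Z > 1.48) + P(Z < −2.44) = 0.069 + 0.007 = 7.7%. If loss is only weakly related to week-4 change (correlation 0.3), the bias is 0.3 × 0.117 = 0.035 SD.

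Simulation (4,000 or more replicates per scenario) agrees:

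| Losses (donepezil/control) | Donepezil losses | Bias, SD of change | t-test type I error |
|---|---|---|---|
| 5/5 | random | 0 | about 5% |
| 5/5 | correlation 0.3 with week-4 change | 0.03–0.04 | 5–6% |
| 5/5 | five worst week-4 changes | about 0.11 | 7–9% |
| 7/3 | seven worst week-4 changes | about 0.15 | 10–11% |
| 10/0 | ten worst week-4 changes | about 0.21 | about 15% |

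The rank test follows the t-test closely: 7.1–7.7% in the third row and 13–14% in the last.

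**4. What the week-4 data recover.** In the rows with selection on week-4 change, a likelihood-type estimate using baseline and week 4 has bias below 0.01 SD. That is so by construction, because loss was made to depend on an observed value. If loss depends on the week-12 change itself, that estimate keeps a bias of 0.16–0.18 SD with five selective donepezil losses and about 0.32 SD with ten.

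**The case against.** **The rank test as a remedy for missing data.** A reader might infer that {18a} offers it as one. Literally, the trigger is failure of parametric requirements, and the sentence sits in a data-collection section. The stronger reading is not supported. What stands is that the fallback leaves missingness untouched and is not reconciled with {20a}, which names only the t-test for the primary outcome.

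**Values filled in by an unblinded investigator.** Section {20c} might suggest this. *Sought and supplemented* can equally mean retrieving entries from source records, and no passage describes entering an unobserved value. The wording needs limiting, but it is not evidence of invented data.

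**Week-12 outcomes lost by rule.** This goes too far. No sentence cancels visit 3 for someone who only stops the drug, and {11a} keeps participants with side effects at the higher dose in the trial to week 12 on the lower one. Only the prohibited-medication rule expressly ends participation, and it can affect either arm.

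**Completers flatter donepezil.** The documents do not support a direction. Nothing links intolerance to a poor fixation ratio, and {12} does not say which direction of the ratio is benefit. Controls who know they are untreated may also withdraw.

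**Left to the analysis plan.** Model choice often is. But here the protocol fixes a test that cannot meet its own statement of who is analysed, and that is a conflict within the document.

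**Conclusion.** The point holds as a should-fix. The stated primary test and its fallback are completers' analyses and cannot meet the all-randomised statement; this follows from the text without any assumption. That week-12 values may be lost after treatment stops, unevenly by arm, is an inference from sections that blur stopping the drug with leaving the trial.

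The size of the harm is conditional. With losses as planned, type I error stays near 5% under random or weakly selective loss and reaches 7–9% under strict week-4 selection in the donepezil arm. The figure near 15% is a stress case and should not be read as expected. The sample size is not in dispute.

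**What to change.** 1. **Primary analysis.** Model the ratio at visits 2 and 3 in all randomised participants with a likelihood-based repeated-measures model (baseline, arm, visit, arm-by-visit), with the week-12 contrast primary. Add a delta-adjusted sensitivity analysis, because the model removes only bias explained by observed data.
2. **Discontinuation {11b} and Prohibited medication.** Separate stopping study drug from leaving the trial. State that the scheduled visit 2 and 3 outcome assessments continue unless consent is withdrawn. No clinical stopping rule needs to change for this.
3. **Section {20c}.** Limit *supplemented* to retrieval from source records.
4. **Sections {18a}, {20a} and the Abstract.** Reconcile them on the primary test.

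The cost is protocol wording and a little more analysis. Visits 2 and 3 are already scheduled for everyone, so there are no added visits or participants. The downside is that some off-treatment data enter the analysis. Item 2 is best done while recruitment continues, since missed week-12 recordings cannot be recovered later.

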### Plans to promote participant retention and complete follow-up {18b}

Participants will be in close contact with each other. There will be scheduled safety checks and frequent contact with the research staff as per the participants’ wish. All randomized participant data will be included in the analysis. If participants withdraw from the study at any stage, they will be asked whether their data accumulated at the point of withdrawal could be included.

### Data management {19}

To promote data quality, participants’ trial data, including cognitive tests, laboratory tests, and medical history, will be summarized in the CRF. These paper CRFs will be stored in the individual participant’s folder. The participants’ data will be kept anonymous in all trial-specific documents, except for signed consent. Each participant’s eye-tracking data and digital pen data will be stored in a trial folder in the electronic database. Participants will be identified only by an identification number on the CRF and any electronic database. All documents will be stored safely under confidential conditions. Data entry will also be supervised by the PI to ensure that there are no transcription errors.

### Confidentiality {27}

The participants’ data will be kept anonymous. Participants will be identified only by the identification number in all trial databases. All documents will be stored securely and accessible to the research staff only. All trial data will be maintained for 5 years after the end of the trial and will be destroyed according to the protocol of the Biomedical Research Institute of Jeonbuk National University Hospital.

### Plans for collection, laboratory evaluation, and storage of biological specimens for genetic or molecular analysis in this trial/future use {33}

In this trial, blood tests, including apolipoprotein E genotyping, will be performed at baseline screening. The samples will be destroyed after analysis, according to the standard protocol. Thus, there is no planned storage for biological specimens.

## Statistical methods

### Statistical methods for primary and secondary outcomes {20a}

As the trial has a parallel design, all analyses will be performed for comparison between the donepezil and control groups. The primary outcome will be analyzed using the two-sample *t*-test, the continuous secondary outcome will be analyzed using the two-sample *t*-test or Mann–Whitney *U* test according to normality, and the ordinal secondary outcome will be analyzed using the Mann–Whitney *U* test. An analysis adjusting for the baseline value will also be performed for each outcome. All results will be presented as mean, median, standard deviation, interquartile range, minimum maximum, and 95% confidence intervals. Sensitivity analyses will be performed to report the robustness of the data.

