**Methods:**

We propose a randomized controlled trial to evaluate the effect of donepezil, a ChEI, on patients with MCI due to AD. We plan to recruit 78 participants (39 in each arm) with MCI who had amyloid positron emission tomography (PET)-positive results for this open-label study. To evaluate subtle differences, we will measure eye-tracking metrics and digital pen data while participants perform the simplified Rey Complex Figure (RCFT) and clock drawing tests. The primary outcome is a change in the ratio of the number of fixations (working space/perceptual space) performed using the simplified RCFT, from baseline to 12 weeks, as assessed using eye-tracking metrics. The secondary outcomes are changes in general cognition, clinical severity, activities of daily living, and visuospatial function assessed using standard rating scores and digital pen data. The analyses of the primary and secondary outcomes will be based on the difference in changes during follow-up between the donepezil and control groups using the *t*-test or Mann–Whitney *U* test, as well as adjusting for baseline values.

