### Outcomes {12}

#### Primary

1. Changes in the ratio of the number of fixations between the two AOIs (working space/perceptual space) performed by the simplified RCFT from baseline to 12 weeks (Fig. 3).

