### Sample size {14}

The sample size was calculated to test differences in the primary outcome between the donepezil and control groups based on the standardized effect size commonly used in clinical studies on cognitive impairment [16, 17]. The standardized effect of donepezil on cognitive tests scores was reported as medium to large size (0.3 ~ 1.9) [18–21]. A recent study showed that fixation frequency had a large effect size (0.8) for the difference between apathetic and non-apathetic AD [22]. This suggests that eye-tracking metrics, such as fixation, might be more sensitive than cognitive scores; therefore, a large standardized effect can be expected in this trial.

A sample size of 34 patients per group achieved 90% power to detect a standardized effect size of 0.8 with a significance level of 0.05, using a two-sided two-sample *t*-test. The standardized effect size of this study was set as the lower bound of the large effect size range (> 0.8) using a conservative approach. Assuming an attrition rate of 12%, a total sample size of 78 (39 patients per group) should be enrolled. The sample size was calculated using PASS 22.0.2.

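### The primary test is an unadjusted t-test on change; an ANCOVA on the baseline ratio would be more precise at no cost, and the abstract and section {18a} disagree with section {20a} on which test is primary.

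*Protocol article*

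**What the plan says.** All references are to the protocol article.

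- **Outcomes {12}, Primary** defines the endpoint, with time counted in weeks: "Changes in the ratio of the number of fixations between the two AOIs (working space/perceptual space) performed by the simplified RCFT from baseline to 12".
- **Statistical methods {20a}** names one test for it: "The primary outcome will be analyzed using the two-sample" t-test. The Mann–Whitney test appears there only for secondary outcomes: as the alternative for continuous ones when normality fails, and outright for ordinal ones ("the ordinal secondary outcome will be analyzed using the Mann–Whitney" *U* test).
- **The same section** then adds: "An analysis adjusting for the baseline value will also be performed for each outcome". It does not say whether this analysis is primary, co-primary or supportive.
- **Abstract, Methods** treats both classes of outcome together: "The analyses of the primary and secondary outcomes will be based on the difference in changes during follow-up between the donepezil and control groups". It goes on to name the t-test or the Mann–Whitney test, together with adjustment for baseline.
- **Plans for assessment and collection of outcomes {18a}** has a further rule: "If the parametric test requirement is not satisfied with the missing data, a non-parametric test will be used". It is not restricted to secondary outcomes, and it does not say how the requirement is judged.
- **Sample size {14}** uses a two-sided two-sample t-test at 0.05 with a standardized effect of 0.8 and 90% power. This gives 34 per arm, or 39 per arm after 12% attrition. The supporting rationale includes a study in which "fixation frequency had a large effect size (0.8) for the difference between apathetic and non-apathetic AD".

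**The concern.** There are two separate issues.

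The first is efficiency. The baseline ratio is measured at visit 1 in all participants. A t-test on change uses it only by subtraction, which is the best weighting only when the baseline to week-12 correlation approaches 1. At any lower correlation, ANCOVA estimates the same treatment effect with a smaller variance and corrects for chance baseline imbalance. Such imbalance is a practical matter with 34 evaluable patients per arm.

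The second is consistency. Section {20a} gives the primary outcome a t-test with no alternative. The abstract and {18a}, read literally, leave a rank test open for it, and the adjusted analysis has no stated rank. In a trial where participants, investigators and staff all know the allocation, the reader should be able to tell from the plan which p-value decides the trial.

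**Working it through.** **Inputs from the article:** d = 0.8, two-sided alpha 0.05, 90% power, 34 per arm, 12% attrition, 1:1 allocation ({14} and Trial design {8}).

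**Assumed:** the correlation rho between the baseline and week-12 ratio is not given, so 0.3 to 0.9 is shown. Variances are taken as equal at both visits.

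**1. The plan's own figure.** Noncentral t, with noncentrality d × √(n/2) and 2n − 2 degrees of freedom:
- n = 33: power 89.3%.
- n = 34: noncentrality 0.8 × √17 = 3.30, power 90.2%.
- 34 / 0.88 = 38.6, so 39 per arm and 78 in total.

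The stated sample size reproduces.

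**2. ANCOVA against the t-test on change, 0.8 in SDs of the change.** With level SD σ, the change has variance 2σ²(1 − rho) and the ANCOVA residual has variance σ²(1 − rho²). Their ratio is (1 + rho)/2, so the effective d for ANCOVA is 0.8 × √(2/(1 + rho)). With 2n − 3 = 65 degrees of freedom:

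| rho | (1 + rho)/2 | effective d | ANCOVA power, 34 per arm | n per arm for 90% |
|---|---|---|---|---|
| 0.3 | 0.65 | 0.992 | 98.1% | 23 |
| 0.5 | 0.75 | 0.924 | 96.3% | 26 |
| 0.7 | 0.85 | 0.868 | 94.1% | 29 |
| 0.9 | 0.95 | 0.821 | 91.5% | 33 |
| t-test on change | – | 0.800 | 90.2% | 34 |

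The gain is about 1 to 8 percentage points of power, or 1 to 11 patients per arm (3% to 32% of 34).

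**3. A smaller true effect.** If the true effect is 0.5 SDs of the change, the t-test has 52.9% power. ANCOVA has 71.2%, 65.0%, 59.6% and 54.9% at rho 0.3, 0.5, 0.7 and 0.9. The gain is larger where the trial is more fragile.

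**4. Which SD the 0.8 refers to.** Section {14} does not say. If it were the SD of the level, the effective d would be 0.8/√(2(1 − rho)) for the t-test on change and 0.8/√(1 − rho²) for ANCOVA:

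| rho | t-test on change | ANCOVA |
|---|---|---|
| 0.3 | 78.4% | 92.6% |
| 0.4 | 84.3% | 94.4% |
| 0.5 | 90.2% | 96.3% |
| 0.6 | 95.3% | 98.2% |
| 0.7 | 98.7% | 99.5% |

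On that reading, the t-test falls short of 90% only when rho is below 0.5.

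**The case against.** The strongest reply is that {20a} is the operative section. It assigns exactly one test to the primary outcome, and {14} powers the trial on that test. The abstract compresses primary and secondary outcomes into one sentence, and the adjusted analysis is worded as an addition, which reads as supportive. Under randomization a t-test on change is valid and unbiased. Most of this stands. The ambiguity comes only from the looser wording of the abstract and {18a}, and the remedy for that is alignment.

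Three stronger readings are tempting and are not supported.

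- **That the type I error is inflated.** If the result could be taken from whichever of t-test, Mann–Whitney and ANCOVA is significant, simulation under the null (34 per arm, normal and lognormal data, rho 0.3 to 0.9) gives about 6.7% to 8.9%. No section permits choosing by p-value. The article describes a switch that depends on normality or on parametric requirements. Simulating such a switch (Shapiro–Wilk at 0.05 in each arm, which is an assumption; 8,000 runs per setting; rho 0.3 to 0.7) gives about 4.8% to 5.5%. The simulation error is about 0.25 points, so this is essentially nominal.
- **That the least efficient standard analysis was chosen.** With equal variances, the t-test on change beats a t-test on the week-12 value alone whenever rho exceeds 0.5. The article does not give rho.
- **That the trial is underpowered because 0.8 comes from a cross-sectional contrast.** Section {14} says the calculation concerns the primary outcome, which is a change. It sets 0.8 as the lower bound of the large-effect range, and the cited contrast is only part of the rationale. Even on the level-SD reading, the shortfall disappears at rho 0.5 and above.

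**Conclusion.** The point holds as an efficiency gain plus a wording conflict; it is not an error that invalidates the design. The planned t-test is valid and meets its stated 90% power at d = 0.8, provided that 0.8 is in SDs of the change. Against ANCOVA it gives up between 1.3 points (rho 0.9) and 7.9 points (rho 0.3) of power at 34 per arm. These figures rest on the assumed range of rho and on equal variances at the two visits. Separately, the abstract and {18a} do not agree with {20a} on the test for the primary outcome, and the adjusted analysis has no stated role. Both matters are worth settling before outcome data are compared by arm.

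**What to change.** - **{20a}:** name ANCOVA of the week-12 fixation ratio, with arm and baseline ratio as terms, as the single primary analysis. Label the t-test on change and the Mann–Whitney test as supportive for this outcome.
- **Abstract, Methods:** describe the primary analysis separately from the secondary ones, in line with {20a}.
- **{18a}:** limit the non-parametric switch to secondary outcomes, or refer to {20a} for the primary one.
- **{14}:** state that 0.8 is in SDs of the change. The calculation of 34 per arm can stay, since ANCOVA has at least 91.5% power across the correlations shown.

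The cost is an amendment of wording. It needs no new data, visits or patients, and the total stays at 78.
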